### Statistical analysis

The primary outcome, superiority of MMF_PK_ over MMF_BSA_ for the percentage of subjects with clinical remission of LN (PRR, CRR) at the end of Part 1, will be tested using the analytical approach for the binomial outcome, such as Chi-square test, Fisher’s exact test, or a Bayesian approach with non-informative Beta prior for the binary probability parameter.

The choice of approach will be determined by the distribution of the data. Subjects who discontinue the treatment due to any reason will be considered as being non-responders. All secondary and exploratory efficacy outcomes will be analyzed by treatment group. For the binary secondary or exploratory outcomes, the analytical approach for the binary outcome, as used for the primary analysis, will be performed.

For the continuous exploratory endpoints, including change from baseline in PROMIS scores or RAIL scores, a mixed-effect model with repeated measures will be applied. The Kaplan-Meier plots will be generated for the exploratory endpoints of time to CRR and time to PRR. Since no measures are collected from the discontinued subject, the analyses will take an Inverse Propensity Weighting (IPW) approach where the propensity for subjects to be discontinued from each arm are estimated using logistic regression modeling or the covariate balance propensity score method.

The IPW approach will create pseudo subject samples that represent the original randomized subject cohort at the beginning of the study, and therefore addresses the missing data issue due to subject discontinuation.

Descriptive/summary statistics for all endpoints, with 95% confidence interval for treatment difference, will be provided. Baseline demographic characteristics, primary and major secondary outcomes will also be summarized overall and by age (<12 years ***vs.*** ≥12 years), gender and race (white ***vs.*** non-white). Safety analysis will be performed on all subjects who received at least one dose of study drug. Safety data will be subject to clinical review and summarized by appropriate descriptive statistics.

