### Randomization

Eligible subjects enrolled in the study will be randomized (1:1) at baseline to receive either MMF_PK_ or MMF_BSA_. Randomization will be stratified by LN class (class 3 or 3/5 ***vs.*** class 4 or 4/5) as per the ISN/RPS and extrarenal manifestations of cSLE (extrarenal SLEDAI score<10 ***vs.*** ≥ 10). Race (white or non-white) and belimumab treatment (yes/no), as well as other important factors which have a known association with long-term outcomes of LN will be considered as potential confounders during the analyses. We will use variable block sizes to ensure balance and to minimize risk for unmasking. Thus, we will be using block sizes of 4 and 2 in random order.

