### Sample size and power estimation

The PLUMM study is the largest clinical trial in pediatric LN, to the best of our knowledge, which is adequately powered. Sample size was determined from a combination of prevalence data and precedents in the literature [13,14,35–43]. A sample size of 45 subjects per group with proliferative LN is anticipated to provide a power of 80% for the primary aim of detecting a significant difference in the rate of PRR between the MMF_PK_ and MMF_BSA_ arms at the end of Part 1, at a 2-sided 5% significance level by a two-group Chi-square test, assuming the rate of PRR is 55% in MMF_BSA_ and 83% in MMF_PK_. The sample size of 90 will ensure 81% of power to detect a statistically significantly difference in the rate of CRR between the two study arms, assuming a smaller proportion of 14% and a larger proportion of 43%. Based on the above presented power analyses, we will plan to enroll 105 subjects, to allow for up to 14.3% attrition rate during Part 1 of the study.

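### The article lets the data choose the primary test, with no criterion and no Bayesian threshold; one stratified test should be named in advance

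*Protocol article*

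**What the plan says.** Protocol article, Statistical analysis: superiority of the PK-guided arm on renal response at the end of Part 1 is to be tested by a binomial method "such as Chi-square test, Fisher’s exact test, or a Bayesian approach with non-informative Beta prior for the binary probability parameter". The next sentence reads "The choice of approach will be determined by the distribution of the data". The section gives no selection criterion, no Beta parameters and no posterior probability that would count as success. Binary secondary and exploratory outcomes, which include CRR, are to be handled as the primary is.

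Sample size and power estimation: power rests on a single test, "at a 2-sided 5% significance level by a two-group Chi-square test", "assuming the rate of PRR is 55% in MMF_BSA_ and 83% in MMF_PK" (the two arms), with 45 per group and 80% power. Planned enrolment is 105, allowing 14.3% attrition.

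Randomization: "Randomization will be stratified by LN class" and by extrarenal SLEDAI (below 10 vs 10 or more), which makes four strata. Race, belimumab and other factors "will be considered as potential confounders during the analyses". No analysis model is given there.

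**The concern.** For a binary outcome in two arms, the data are the responder counts. A rule that picks the test from their distribution, with no stated criterion, leaves the confirmatory decision rule open until the counts exist. The candidates do not have the same power, and the Bayesian one has no operating characteristics at all until a threshold is set. The two-sided 5% level appears only in the power calculation, while the primary hypothesis is worded as superiority of one arm.

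This is a stated rule and not a detail left to the analysis plan: a plan that named one test would contradict the article's sentence. In addition, none of the three named tests, as described, uses the factors on which randomisation is stratified.

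**Working it through.** **Inputs.** From the article: 45 per arm, 55% vs 83%, two-sided 5%, 105 enrolled, 14.3% attrition, treatment discontinuation counted as non-response, four strata. Assumed because the article does not give them: Beta(1,1) prior, posterior threshold of 0.975 or 0.95, prognostic odds ratio (OR) per factor, and stratum sizes.

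**1. The article's own figure.** Pooled chi-square, mean rate 0.69:

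z = [0.28·√45 − 1.96·√(2·0.69·0.31)] / √(0.55·0.45 + 0.83·0.17) = (1.878 − 1.282)/0.623 = 0.957, so power is 83.1%.

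The stated 80% is not matched exactly, but rounding of the rates could explain it (55.5% vs 82.5% gives 80.1%). The sample size is not too small for this test.

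**2. Exact power by test.** Power = Σ Bin(a; n₀, p₀)·Bin(b; n₁, p₁) over all tables (a, b) that reject. At 45 per arm, 55% vs 83%:

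| Test | Power | Type I error, common rate 55% | Type I error, common rate 69% |
|---|---|---|---|
| Chi-square | 84.4% | 4.6% | 5.4% |
| Fisher | 77.7% | 2.8% | 3.0% |
| Beta(1,1), 0.975 either way | 83.4% | 4.4% | 4.9% |
| Beta(1,1), one-sided 0.95 | 89.9% | 5.6% | 4.8% |
| Best of three, 0.975 | 84.4% | 4.6% | 5.4% |
| Best of three, one-sided 0.95 | 89.9% | 7.9% | 7.4% |

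At 52/53 per arm and a common 55%, the best of three with the one-sided 0.95 rule gives 7.6%.

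**3. Conflicting verdicts.** Under the planned effect at 45 per arm, chi-square rejects and Fisher does not in 6.7% of trials. Example: 25/45 vs 34/45. z = 0.200/√(0.6556·0.3444·2/45) = 0.200/0.1002 = 2.00, p = 0.046; Fisher p = 0.075.

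**4. At planned enrolment.** With 52 BSA and 53 PK subjects: chi-square 88.7%, Fisher 87.2%, a gap of 1.5 points. Counting 14.3% attrition as non-response dilutes the rates to 0.55·0.857 = 47% and 0.83·0.857 = 71% (an assumption about who drops out): 71.2% vs 68.8%, a gap of 2.4 points. The gap depends on the exact split, because Fisher is more conservative with equal arms: at 52/52 it is 88.8% vs 83.6%, or 5.2 points.

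**5. Is there a sparse-data reason to keep Fisher open?** The smallest expected count at 45 per arm is 45·(1 − 0.69) = 14 for PRR and 45·0.285 = 12.8 for CRR (14% vs 43%). There is none at the planned rates.

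**6. Strata.** Simulation with N = 90, four equal strata, marginal rates held at 55% and 83%, 100,000 trials per setting:

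| OR per factor (assumed) | Power: chi-square / CMH | Difference | Type I error: chi-square / CMH |
|---|---|---|---|
| 1 | 84.3 / 83.6% | −0.7 | 4.5 / 4.6% |
| 2 | 84.6 / 85.0% | +0.4 | 4.1 / 4.9% |
| 3 | 85.3 / 87.2% | +1.9 | 3.3 / 4.9% |
| 5 | 86.6 / 90.3% | +3.7 | 2.5 / 5.0% |

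Across the other stratum splits tried, the loss at OR 1 is at most 0.8 points, the gain at OR 5 is about 3 to 4 points, and the chi-square type I error at OR 3 is 3.3 to 3.5%.

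**The case against.** **The usual reading is harmless.** Choosing Fisher when expected counts are small depends on the pooled responder total and the arm sizes, not on the difference between arms. At the planned rates such a rule would essentially never trigger. In every setting enumerated, neither Fisher nor the 0.975 Bayesian rule rejected where chi-square did not. This stands: a reader might infer that the sentence by itself inflates the false positive rate, and the article does not support that. But it does not state the small-count rule either, and that rule would not say when to use the Bayesian analysis.

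**The 0.95 rule is not in the article.** True. It is an assumption that shows what an unset threshold allows. The 7.5 to 7.9% is therefore a possibility the text leaves open, not a property of the plan.

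**The strata may be handled elsewhere.** The list of tests is open-ended, and a full protocol or analysis plan may specify a stratified model. A reader might infer that the plan gives up power by ignoring the strata, or that it breaks a commitment to adjust for covariates. Neither is shown. The strength of the factors is not given, CMH loses slightly if they are weak, and supportive models would satisfy the sentence on confounders. CMH over these two factors would not adjust for race or belimumab anyway.

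**Conclusion.** The point holds as a defect in how the decision rule is fixed. The article ties the primary test to the observed data without a criterion, leaves the Bayesian success threshold unset, and departs from the single test on which it is powered. Power ranges from 77.7% to 89.9% at 45 per arm, depending on the test and threshold. Near planned enrolment the Fisher penalty is smaller: 1.5 points at 52/53, 2.4 points at the diluted rates, and up to 5.2 points if the arms are exactly equal. Type I error stays at the chi-square level with a 0.975 threshold and reaches about 7.5 to 7.9% (common rate 55%) only under an assumed one-sided 0.95 rule.

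On the strata the conclusion is conditional. If they are prognostic, the unstratified test is conservative (about 3.5% actual type I error at an assumed OR of 3 per factor, against about 5% for CMH). The effect of CMH on power runs from about −0.8 to +4 points over OR 1 to 5. That makes CMH a nearly free improvement, not the repair of an error.

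**What to change.** Replace the sentence on choice of approach with one pre-specified primary analysis:

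- CMH test of PRR at week 26, stratified by LN class (3 or 3/5 vs 4 or 4/5) and extrarenal SLEDAI (below 10 vs 10 or more), two-sided 5%, all randomised subjects, with the Mantel-Haenszel risk difference and its 95% confidence interval.
- A numeric rule for collapsing the extrarenal factor: a stated minimum stratum size, counted over both arms together and set before unblinding.
- The same method for CRR.
- Chi-square, Fisher and the Beta-binomial analysis (prior stated, posterior threshold 0.975) labelled as sensitivity analyses.

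The cost is wording in the protocol and analysis plan. The strata are already recorded at randomisation and no new data are needed. The downside is a loss of under 1 point of power if the strata turn out not to be prognostic.

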## METHODOLOGY

### Design

This is a randomized double-blind active comparator clinical trial of pediatric subjects (8 to<18 years of age) with proliferative LN as per the International Society of Nephrology/ Renal Pathology Society (ISN/PRS) classification criteria [21]. All eligible subjects are randomized at baseline to one of 2 arms: the current standard of clinical care (MMF_BSA_) or pharmacokinetically-guided precision dosing (MMF_PK_). Subjects in the MMF_BSA_ arm who achieve PRR at week 26 will be switched to the MMF_PK_ arm. At the end of Part 1, subjects in the MMF_PK_ arm with CRR or PRR or MMF_BSA_ arm subjects with CRR will continue their respective treatment arms during Part 2 of the study. At week 26 (end of Part 1) treatment non-responders, i.e. subjects who did not achieve PRR at week 26, will be discontinued from active medication management in the study but will still be monitored for a total of 53 weeks. The MMF starting dose for both treatment arms will be the recommended MMF dose for pediatric LN at 600 mg/m^2^ twice daily, about 12 hours apart [22]. Only in the MMF_PK_ arm will the MMF dose be adjusted for a target MPA-AUC_0–12_ of 60 mg*h/L, with initial Bayesian PK-profiling performed after drug steady state is achieved. A schema of the study design is shown in Figure 2.

The study is overseen by a Centralized Coordinating Center (CCC), a study steering committee which includes a representative of the Lupus Foundation of America, and an independent Data Safety Committee that was selected by the National Institute of Arthritis and Musculoskeletal and Skin Diseases (NIAMS).

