Notably, the SSR has been specifically developed for the PLUMM study in an international effort that used state-of-the art consensus methodology, statistical modeling, and true disease courses of children with LN. In brief, the SSR considers the time since LN diagnosis, the course of LN and extrarenal SLE, as well as the prior CS dosage since the preceding clinical assessment of the subject to suggest the dose of oral prednisone or IV methylprednisolone. Standardization of CS use is important, as CS are potent effect modifiers that require careful dosing in any randomized clinical trial of an inflammatory disease and has been identified to be one of the significant factors impacting the success of clinical trials in lupus [45,46]. This SSR is anticipated to manage and reduce variability of CS dosage using international consensus and real-life cSLE patient data.

The study design has some limitations. The feasibility of recruitment may be affected by the need in some patients for therapy with IV cyclophosphamide and/or B-cell depletion therapy (rituximab or belimumab). If such is deemed necessary for the treatment of a patient leading to their discontinuation of the study, their clinical outcome will still be monitored longitudinally. Concurrent use of calcineurin inhibitors may also affect MPA PK, so a subanalysis may be performed in those patients receiving this. Given the complex clinical course of cSLE patients, variability in CS dosing may persist despite SSR use, leading to potential deviation from the proposed standardized steroid regimen. If this was to be the case, then we will correct analyses for variation in CS dose and consider Bayesian analysis with causal interference strategies to correct for the CS effect. Since high doses of CS decrease exposure to MPA, we will repeat MPA PK measurement if a patient’s CS dose has changed by>50% or>20 mg since the last MPA PK profile. MPA PK may also be affected by concurrent medications. However, these will be kept stable during the study, other than CS.

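### Inverse weighting of the exploratory week-53 analyses rests on a no-data premise that the article contradicts, and cannot recover week-26 non-responders

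*Protocol article*

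**What the plan says.** The Statistical analysis section plans a repeated-measures mixed model for the continuous exploratory endpoints. For the time-to-event endpoints it says: "The Kaplan-Meier plots will be generated for the exploratory endpoints of time to CRR and time to PRR". The reason for weighting follows directly: "Since no measures are collected from the discontinued subject, the analyses will take an Inverse Propensity Weighting (IPW) approach". The weights come from a model in which "the propensity for subjects to be discontinued from each arm are estimated using logistic regression modeling or the covariate balance propensity score method", and the stated result is that weighting will "create pseudo subject samples that represent the original randomized subject cohort at the beginning of the study". The covariates are not named.

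Two other places describe what happens to discontinued subjects:

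- Design: at the end of Part 1, "treatment non-responders, i.e. subjects who did not achieve PRR at week 26, will be discontinued from active medication management". The same sentence says that these subjects "will be discontinued from active medication management in the study but will still be monitored for a total of 53 weeks".
- Discussion, on subjects who leave for cyclophosphamide or B-cell therapy: "their clinical outcome will still be monitored longitudinally".

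The outcome section lists RAIL change and time to PRR and CRR as exploratory, running from baseline to week 53. For the response outcomes, the Statistical analysis section has a separate rule: anyone who discontinues treatment counts as a non-responder.

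**The concern.** There are two problems, and they are alternatives rather than additive.

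First, the stated reason for weighting does not agree with the follow-up described elsewhere. If the Design and Discussion are right, the data exist and the plan would set them aside.

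Second, if the data do not exist, weighting cannot replace them after week 26. Inverse weighting needs every kind of subject to have some chance of remaining. Under the Design rule, a subject without PRR at week 26 has none. No continuing subject resembles them on the variable that decided their exit, so no set of weights on the continuers can represent the randomized cohort.

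At stake are the exploratory comparisons that extend past week 26: RAIL, quality of life and time to CRR. The excluded group is selected by outcome and is expected to be larger in one arm, so any distortion would differ between arms.

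**Working it through.** **The plan's own figure.** Enrolment of 105 with 14.3% attrition leaves 105 × (1 − 0.143) = 89.99, or 90 subjects, which reproduces. That allowance is for attrition during Part 1. It does not cover the week-26 rule.

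**How many subjects the rule removes.** Inputs from the sample size section: PRR 55% (BSA) and 83% (PK), 45 per arm.

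- BSA: 1 − 0.55 = 0.45; 45 × 0.45 = 20.25.
- PK: 1 − 0.83 = 0.17; 45 × 0.17 = 7.65.
- Total: 27.9 of 90, or 31%.

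**Can weighting work after week 26?** The probability of continuing given no PRR at week 26 is 0 in both arms, so the inverse weight is 1/0. There are two ways to build the propensity model:

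- *With week-26 response.* The model separates. In a simulated arm of 45, the fitted probabilities of continuing for non-responders were between about 1e-17 and 1e-16.
- *Without it.* The model fits, but responders are weighted up to stand in for non-responders.

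The second case was simulated with 400,000 subjects per arm and a baseline-only propensity model. By assumption, responders scored 1 SD better at week 53 (lower is better), and 5% of responders were lost at random.

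| Mean at week 53 | BSA | PK | PK − BSA |
|---|---|---|---|
| All randomized | −0.549 | −0.830 | −0.281 |
| Continuers, unweighted | −1.084 | −1.034 | +0.050 |
| Continuers, weighted | −1.001 | −1.001 | 0.000 |

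In general, let d be the responder benefit, equal in both arms, with all benefit acting through response. The true difference is then (0.83 − 0.55) × d = 0.28d, and a weighted continuers-only comparison gives about 0. The loss is 0.14, 0.28 or 0.42 SD for d = 0.5, 1.0 or 1.5 SD.

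**Time to CRR.** Week-26 CRR is taken as 14% (BSA) and 43% (PK). The article calls these the smaller and larger proportions, and assigning them to the arms is my reading. PRR without CRR is 0.55 − 0.14 = 0.41 and 0.83 − 0.43 = 0.40. Assume that 30% of this group reaches CRR by week 53 in each arm. Let q be the proportion of week-26 non-responders who do so later.

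- True BSA: 0.14 + 0.41 × 0.30 + 0.45q = 0.263 + 0.45q.
- True PK: 0.43 + 0.40 × 0.30 + 0.17q = 0.550 + 0.17q.
- True difference: 0.287 − 0.28q.
- Kaplan-Meier with non-responders censored at week 26: 1 − 0.86 × 0.70 = 0.398 and 1 − 0.57 × 0.70 = 0.601, a difference of 0.203.
- Understatement: 0.287 − 0.28q − 0.203 = 0.084 − 0.28q.

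This is 8.4 points at q = 0 and 0 at q = 0.30. Above 0.30 the sign reverses.

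**Time to PRR.** The subjects censored at week 26 are exactly those without PRR, and those who continue have already had the event. Censoring cuts the curve off at week 26 but does not distort it before then.

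**The case against.** The strongest reply is that little of importance is touched. The week-26 primary and major secondary outcomes count discontinued subjects as non-responders. CRR at week 53, a binary secondary outcome, is to be analysed in the same way as the primary. This stands: a reader might infer that the trial's main comparison is biased, and the document does not support that.

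Several other stronger readings also fail:

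- *That weighting cannot work at all.* It fails only for data after the week-26 rule. For sporadic dropout in Part 1 it remains usable, and its covariates may properly be left to the SAP.
- *That time to PRR is biased.* As shown above, it is truncated.
- *That 8.4 points or 0.28 SD is the bias.* The first figure needs no later conversion among non-responders, who remain monitored and may receive other therapy. The second describes a continuers-only comparison at week 53. The plan specifies a repeated-measures model, and if discontinued subjects' scores up to week 26 enter it, the loss is smaller.
- *That censoring at week 26 is stated.* It is not. It follows only if the no-data premise is applied.

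It can also be said that stopping study medication differs from leaving the study, and that monitoring need not include RAIL or questionnaires. That is fair for those measures. It does not rescue the premise, because renal response is a clinical outcome and the Discussion promises to follow clinical outcome in subjects who leave the study.

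**Conclusion.** The point holds for the exploratory endpoints after week 26. The premise that discontinued subjects provide no measures conflicts with the Discussion and, on its natural reading, with the Design section. If the premise were true, the claim that weighting restores the randomized cohort would still be wrong after week 26, because response determines who stops. On the planning rates that concerns about 28 of 90 subjects, 45% of one arm and 17% of the other.

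The size of the bias cannot be fixed from the document. For time to CRR, the understatement runs from 8.4 to 0 points as later conversion among non-responders goes from 0% to 30%, given 30% conversion among subjects with PRR only. For continuous scores it is at most about 0.28 times the assumed responder benefit under the model above, and less if earlier data enter the mixed model.

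The Abstract says that subjects who achieve PRR at week 26 stop study intervention, whereas Design applies this to those who do not. The two must be reconciled. Either wording makes stopping certain for a whole response class, so neither rescues the weighting. This should be fixed, at a severity suited to exploratory endpoints.

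**What to change.** 1. Delete the statement that discontinued subjects contribute no measures, and state which assessments are collected after discontinuation and until when.
2. Analyse by randomized arm all assessments collected through week 53, including those after discontinuation.
3. For time to CRR, keep week-26 non-responders in the risk set using their monitored data. Alternatively, report cumulative incidence with discontinuation as a competing event and say that this answers a different question, namely CRR reached before discontinuation.
4. Limit weighting to true loss to follow-up, with post-baseline renal measures in the model, and drop the claim that it restores the randomized cohort after week 26.
5. If RAIL or quality of life will not be collected after week 26 in non-responders, end those between-arm comparisons at week 26.
6. Reconcile the Abstract and Design on who is discontinued at week 26.

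The cost is protocol and SAP wording plus modest programming. The clinical follow-up is already promised, and no sample size figure changes. Sites should be told early, because assessments not made cannot be recovered.
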